### Recruitment {15}

Pregnant women with depressive symptoms are recruited by an advertisement repeatedly shared in social media by the Department of Obstetrics and Gynecology in Turku University Hospital and by brochures distributed during routine ultrasound scans. The recruitment advertisement includes a link to the research project’s web page, where the pregnant women can fill out an electronic EPDS questionnaire and provide their contact information. The research team’s doctoral student phones those women who have received 10-15 points on the EPDS questionnaire in order to recruit them. During the first contact, the doctoral student ensures that the women meet the inclusion criteria, interviews them with Structured Clinical Interview for Diagnostic and Statistical Manual of Mental Disorders (DSM)-IV-TR (SCID), and makes an appointment for the first attachment representation interview (Working Model of the Child Interview [WMCI]). The doctoral student also contacts the women who have received 16 or more on the EPDS questionnaire or reported suicidal thoughts in order to identify their need for support.

Due to the COVID-19 pandemic, the recruitment was suspended from March 16 to September 22, 2020, but has continued since then.

## Assignment of interventions: allocation

### Sequence generation {16a}

Randomization for the intervention and the control groups was performed with random permuted blocks, using block size 10. SAS® was used to generate the randomization (Version 9.4 for Windows, SAS Institute Inc., Cary, NC, USA), and programming was done by a biostatistician.

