**Methods:**

A controlled randomized setting was designed to assess whether interactive 4D-ultrasound intervention would decrease maternal depressive symptoms, strengthen maternal-fetal attachment, and mother-infant relationship. An obstetrician and a psychologist specialized in infant mental health conduct the interventions. The focus is to jointly observe the behavior of the fetus according to the mothers’ wishes. Altogether, 100 women scoring 10–15 on Edinburgh Pre-/Postnatal Depression Scale (EPDS) and with singleton pregnancy are recruited using a web-based questionnaire. Half of the participants will be randomized to the intervention group and will undergo three interactive ultrasound examinations. The primary outcomes are a decrease in perinatal depressive symptoms assessed with EPDS and an increase in maternal attachment. The maternal attachment was assessed using the Working Model of the Child Interview (WMCI), the Maternal Antenatal Attachment Scale (MAAS), and the Maternal Postnatal Attachment Scale (MPAS). Secondly, we hypothesize that if the intervention decreases prenatal depressive symptoms and improves prenatal attachment, the decrease in depressive symptoms and improvement in mother-infant relationship is seen postnatally.

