## Methods: participants, interventions, and outcomes

### Study setting {9}

In Finland, over 99% of all pregnancies are monitored in Healthy Maternity Clinics [63] that are part of the basic healthcare arranged by the municipalities. The clinics provide screening for fetal chromosomal abnormalities at the end of the first trimester and for severe structural abnormalities between 19 and 21 gwks, as well as offer family support, with attention to relationships and parenting. Risk pregnancies are also referred to maternity outpatient clinics in hospitals. Deliveries and conditions requiring emergency care are treated in hospitals as well. The Finnish health care system supports women experiencing miscarriage, stillbirth, or adverse pregnancy outcomes [64]. The perinatal mortality rate in Finland was 0.4% in 2019 [65].

This study is carried out at the Hospital District of Southwest Finland, at the maternity clinic of Turku University Hospital, and in collaboration with the Department of Psychology, University of Turku. This tertiary level hospital offers extensive specialized health care services to the residents. There are approximately 4000 births annually; in 2020, there were 3811 births [66].

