### Sample size {14}

The study aims to compare changes in EPDS scores between two independent groups. A mean decrease of three points in the EPDS score is considered clinically relevant and used for power calculations. A standard deviation (SD) of 3.5 points in the EPDS score used in power calculations was based on earlier studies in the Finnish population showing an SD of 3.7–4 [25]. A power analysis using a statistical power of 80% and a significance level of 0.05 (two-tailed) showed that 50 subjects are needed in both groups. Because of an estimated attrition rate of 10%, 60 subjects for both groups are currently being enrolled. Randomization was performed with random permuted blocks, using block size 10. The SAS® was used to generate the randomization (Version 9.4 for Windows).

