### Concealment mechanism {16b}

The randomization list is kept in a locked place to which only the study group has access. After the first attachment representation interview, the interviewer looks at a separate randomization list to find out the group to which the participant is assigned and reveals it to the participant. Two graduate students of psychology carry out the interviews, which are scheduled according to the gestational weeks of the participants.

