## Assignment of interventions: blinding

### Who will be blinded {17a}

Blinding of the coders of the representation interviews and the mother-infant interaction is important for avoiding bias. However, two coders who rate the attachment representation interviews are not completely blinded, because one of them is a member of the intervention team. To avoid bias, the coder who rates the second representation interview does not know the group to which the participant belongs. However, the participants may talk about the intervention visits during their post-intervention interview, thus revealing their group allocation.

Similarly, the coders of the mother-infant interaction situations are not completely blinded. Oner is the main coder, doing 100% of the codings, and is not completely blinded to the sample because she has interviewed some participants and may thus know their study group status. However, the reliability coder, who does 25% of the codings overlapping those done by the main coder, is completely blinded for the group status.

The participants know to which group they belong, which is also a potential source of bias. However, in the informed consent form, they are not exactly told about the primary outcomes of the study.

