## Trial

The protocol version number is five as of December 7, 2021. The first participant was recruited on September 19, 2018. By December 7, 2021, 66 participants have been recruited. The recruitment will be completed within 2 years.

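### A fixed, published block size of 10 in a one-centre open trial lets an interviewer who keeps count deduce on average one assignment in six

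*Protocol article*

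**What the plan says.** The Protocol article fixes one block size in two places: "Randomization for the intervention and the control groups was performed with random permuted blocks, using block size 10" (Sequence generation {16a}) and "Randomization was performed with random permuted blocks, using block size 10" (Sample size {14}). Neither section names strata or varied block sizes.

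The allocation ratio is 1:1: "Half of the participants will be randomized to the intervention group and will undergo three interactive ultrasound examinations" (abstract, Methods). There is one centre: "This study is carried out at the Hospital District of Southwest Finland, at the maternity clinic of Turku University Hospital" (Study setting {9}).

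Allocation is open: "The participants know to which group they belong, which is also a potential source of bias" (Who will be blinded {17a}). It is also handled by the interviewers, once the baseline WMCI is complete: "the interviewer looks at a separate randomization list to find out the group to which the participant is assigned and reveals it to the participant" (Concealment mechanism {16b}). The section on informed consent {26a} has the same graduate students collecting the consent forms at the start of that visit.

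Recruitment was still open when the block size was published: "By December 7, 2021, 66 participants have been recruited" (Trial), with "60 subjects for both groups are currently being enrolled" (Sample size {14}).

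**The concern.** With a fixed, known block size, each block must end with five women in each arm. Once one arm has its five, every later assignment in that block is known. Before that, the arm with fewer women so far is the better guess. In an unstratified open trial at one centre, a running tally is enough. Locking the list away does not prevent this, because the past allocations are themselves known.

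The people who certainly hold this information are the two graduate students. Before the next allocation they collect consent and conduct the baseline WMCI. Prenatal representations before and after the intervention are part of the primary outcome (Outcomes {12}). If an interviewer can foresee the arm, encouragement to consent or the conduct of the baseline interview could differ by arm. Later blinding gives limited cover: EPDS is self-reported by women who know their group, and Who will be blinded {17a} concedes that the interview coding is not completely blinded.

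**Working it through.** The plan gives no predictability figure, so there is none to reproduce.

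**Inputs.** Block size 10 (Sequence generation {16a}); half of the women per arm (abstract), so 5 + 5 per block; 60 per group, so 120 women or 12 blocks (Sample size {14}); 66 recruited (Trial).

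**Certain assignments.** There are C(10,5) = 252 equally likely blocks. Assignment k is certain if one arm has already reached five, which happens in 2 × C(k−1, 5) of them.

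| Position k | 1–5 | 6 | 7 | 8 | 9 | 10 |
|---|---|---|---|---|---|---|
| Blocks out of 252 | 0 | 2 | 12 | 42 | 112 | 252 |
| Chance of certainty | 0% | 0.8% | 4.8% | 16.7% | 44.4% | 100% |

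The sum is 420/252 = 1.67 per block. The closed form for a block of 2n agrees: 2n/(n+1) = 10/6 = 1.67. The share is 1.67/10 = 1 in 6, which gives 120/6 = 20 women. If the total is the 100 of the abstract, it gives 100/6 = 16.7.

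**Best guess.** An observer who always names the arm with fewer women so far, and tosses a coin at a tie, expects n + 2^(2n−1)/C(2n,n) − 0.5 correct guesses per block. For n = 5 this is 5 + 512/252 − 0.5 = 6.53 of 10, or 65.3%.

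**What is left to protect.** Six full blocks cover 60 women and the seventh ends at 70. That leaves 120 − 70 = 50 women, or 100 − 70 = 30 on the abstract's total. Under the present scheme 50/6 = 8.3 of the 50 would be certain.

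**Alternatives.** The correct-guess rates other than the first come from simulating 50 further women. The certain shares for varied blocks come from simulating 120 assignments with an observer who knows the possible sizes and all past allocations.

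| Scheme | Correct guesses | Certain assignments |
|---|---|---|
| Fixed 10 (plan) | 65.3% | 16.7% |
| Random sizes 4–10 | about 67% | 2.3% for 4/6/8; 1.6% for 6/8/10 |
| Random sizes 10–20 | about 62% | not computed; 1.3% for 8/10/12 |
| Big stick, limit 6 | about 53% | about 6%, and only if the limit is known |

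Varied blocks remove most certain deductions but hardly lower the guess rate. Every block still returns to balance, so the arm that is behind remains the better guess.

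Under the big-stick rule each assignment is a fair coin toss unless the limit is reached. With 6.2% forced, the correct-guess rate is 0.062 + 0.938 × 0.5 = 0.531.

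**Price of the big-stick rule.** The mean final difference in arm sizes is about 3 women. Relative efficiency with 120 women is 1 − (3/120)² = 0.9994. At the limit of 6 it is 1 − (6/120)² = 0.9975.

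**The case against.** - **The list itself is the larger exposure.** Concealment mechanism {16b} and Implementation {16c} let the interviewers read the sequence, and the study group has access to it. Nobody with that access needs to count blocks. This stands: a new sequence read in the same way gains nothing, so the remedy must include single release. It does not remove the point, because curing list access alone would leave the block tails countable.
- **A reader might infer that the whole recruiting team knows every past allocation.** The document does not support that. The doctoral student phones, screens and conducts the SCID; the graduate students read the list. Whether the doctoral student learns past allocations is not stated. First interviews are scheduled by gestational week, so the order of phone calls does not fix a woman's place in the sequence. The point therefore rests on the graduate students' part in consent and the baseline interview.
- **A reader might convert the guess rate into EPDS points of bias in the primary result.** That needs a size of steering that the document does not give. The screening EPDS is completed on the web page before any contact, and entry is limited to 10–15 points. The analysis concerns change over time through the time-by-intervention interaction, so a shift in baseline level would not carry over one for one. No such figure is claimed.
- **A fixed block of 10 is a legitimate choice.** It is less predictable than a fixed block of 4 (33% certain) or 6 (25%). It also keeps the arms balanced over calendar time, which has some value in a trial that started in September 2018, paused from March to September 2020 and then allowed remote interviews. Both stand, and they limit the weight of the point.

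**Conclusion.** The point holds as a preventable weakness and a low-cost improvement. It is not evidence that selection occurred: nothing in the document shows that anyone used the predictability.

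Its size is 1 in 6 assignments certain on average (about 20 of 120) and 65% correct guesses against 50% by chance. This assumes 5 + 5 in every block, an interviewer who keeps a tally, and a single sequence. That there are no strata rests on none being named. If each interviewer has a separate list, the share is still 1 in 6 within each list. The 70 and 50 women are approximate, because recruitment precedes randomisation and the count dates from December 2021.

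**What to change.** At the end of the current block (about 70 women), have the biostatistician generate a new 1:1 sequence for the roughly 50 remaining women.

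- **Preferred:** a big-stick rule with a maximum imbalance of about 6.
- **Second choice:** block sizes varied at random, for example 10 to 20. This removes most certain deductions but lowers the correct-guess rate only from 65% to about 62%. Smaller sizes such as 4 to 10 also cut certain deductions but leave the guess rate at about 67%.

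With either, keep the block sizes or the imbalance limit from the recruiting and interviewing team, and publish them only after recruitment ends. Release each assignment singly, after the baseline interview is complete, instead of letting interviewers consult the list. This last step is essential.

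The cost is one new SAS list, a way of releasing single assignments, and a protocol amendment accepted by the Ethics Committee. The statistical price is a possible final difference of about 3 women between the arms and slightly less balance over calendar time.

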### Concealment mechanism {16b}

The randomization list is kept in a locked place to which only the study group has access. After the first attachment representation interview, the interviewer looks at a separate randomization list to find out the group to which the participant is assigned and reveals it to the participant. Two graduate students of psychology carry out the interviews, which are scheduled according to the gestational weeks of the participants.

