### Who will take informed consent? {26a}

An information letter, which can be found on the project’s webpage is emailed to the women who have completed the depression screener through the webpage. The graduate students in psychology collect the informed consent forms from the participants at the beginning of the first study visit, which is the attachment representation interview.

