### Implementation {16c}

A biostatistician carried out the allocation sequence before the start of the present randomized study. The doctoral student contacts potentially eligible women to recruit them, ensures that they meet the inclusion criteria, conducts an SCID interview, and makes an appointment for the first attachment representation interview. The graduate students of psychology conduct the first WMCI- interview, they then look at the allocation sequence to find out the group the participant is assigned. Two graduate students work on the project simultaneously and have received training to follow the study protocol.

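### The described procedure does not secure allocation concealment: the people who collect consent and hold the baseline interview look up the group themselves on a pre-generated list

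*Protocol article*

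**What the plan says.** Four parts of the protocol article describe the route from consent to allocation.

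- **Sequence.** Sequence generation {16a} specifies "random permuted blocks, using block size 10". Implementation {16c} adds: "A biostatistician carried out the allocation sequence before the start of the present randomized study".
- **Custody.** Concealment mechanism {16b}: "The randomization list is kept in a locked place to which only the study group has access".
- **Consent and baseline interview.** Who will take informed consent? {26a}: "The graduate students in psychology collect the informed consent forms from the participants at the beginning of the first study visit". That visit is the first WMCI. On the interviews, {16b} says: "Two graduate students of psychology carry out the interviews".
- **Look-up.** After the interview, according to {16b}, "the interviewer looks at a separate randomization list to find out the group to which the participant is assigned" and then tells the participant. Implementation {16c} describes the same step: "they then look at the allocation sequence to find out the group the participant is assigned".

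Recruitment is a separate role. Implementation {16c}: "The doctoral student contacts potentially eligible women to recruit them, ensures that they meet the inclusion criteria"; the same person also conducts the SCID and makes the appointment.

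**The concern.** Concealment requires that nobody who enrols or assesses a woman can know her group until she is irrevocably in the trial and her baseline data are fixed. Here the stated barrier keeps outsiders away from the list, while those who most need to be kept from it are the ones who consult it.

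For any one woman the order is right: consent, interview, then look-up. The weakness lies between women. An interviewer who reads one line may see the next before the next woman signs and is interviewed.

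Two things are then at stake. The first is whether a woman signs at the visit, which would be selection bias. The second is how the semi-structured baseline WMCI is conducted. Outcomes {12} counts prenatal representations before and after the intervention as part of the primary outcome, so a baseline interview coloured by the expected group would distort a primary comparison. Neither can be reliably repaired in the analysis. Participants know their group and the coders are not completely blinded (Who will be blinded {17a}), so concealment is one of the few protections left.

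**Working it through.** The protocol gives no figure to reproduce. The check is a side-by-side reading, followed by a calculation for the block size.

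**1. Can the next assignment be seen?**

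| Question | Text | Consequence |
|---|---|---|
| Does the full sequence exist in advance? | Yes ({16c}) | Future lines exist to be seen |
| What is consulted? | A separate randomization list ({16b}); the allocation sequence ({16c}) | A list, not a single released assignment |
| Who consults it? | The interviewers ({16b}, {16c}) | The same role that collects consent ({26a}) and holds the baseline WMCI |
| When? | After each woman's own interview ({8}, {16b}) | Protects her only if her line was not seen earlier |
| What prevents sight of later lines? | A locked place open to the study group ({16b}) | Nothing stated: no masking, envelopes, central release or independent holder |

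Two students work on the project at the same time ({16c}), so the list is opened repeatedly.

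**2. What does the fixed block size add without sight of later lines?**

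Inputs: block size 10 ({16a}); 1:1 blocks, so k = 5 per arm, which is an assumption drawn from the equal group sizes in Sample size {14}. No strata are stated.

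- Assignments certain in advance, because one arm is already used up: 2k/(k+1) = 10/6 = 1.67 per block, or 16.7%. Enumerating all C(10,5) = 252 balanced blocks gives the same value. Over 120 women (12 blocks) this is 1.67 × 12 = 20.
- Correct guesses when always guessing the arm with more places left: k + ½[2^(2k)/C(2k,k) − 1] = 5 + ½(1024/252 − 1) = 6.53 per block, or 65.3%, against 5 of 10 by chance. The enumeration agrees. Over 120 women this is about 78.

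Both figures require one person to know the block size, the position in the block and every past assignment, including those looked up by the other interviewer. The list itself is therefore the main exposure.

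**3. How many women can still be protected?**

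The section headed Trial reports 66 recruited by December 7, 2021. The target is 120 in Sample size {14} and 100 in the abstract. If all 66 had been randomized, 120 − 66 = 54 (45%) or 100 − 66 = 34 would remain. Recruited is not randomized, because randomization follows the first interview. At that date the number not yet randomized may have been larger.

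**The case against.** The strongest reply is that the route to bias is narrow, and much of that stands.

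- The doctoral student, not the interviewers, phones the women, checks eligibility, conducts the SCID and books the visit. Women have agreed to take part and been sent the consent document before they meet an interviewer. Selective consent would mean losing a screened and booked woman at the visit. However, the doctoral student belongs to the research team and is not stated to be excluded from list access.
- Scheduling by gestational week limits reordering.
- EPDS, on which the sample size rests, and MAAS are self-reported through REDCap. Only the WMCI depends on the interviewer, and it follows a trained protocol and is rated from recordings under a manual.
- The layout of the list is not described. The word separate in {16b} could mean something other than an open copy of the sequence. Visibility of later lines is an inference.

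A reader might go further and infer that every assignment is foreseeable. The text does not support this, because it does not show what the interviewer sees. A reader might also infer that the same two students collect all later outcomes. The sections on the WMCI and on mother-infant interaction name only the role, graduate students in psychology, and two working simultaneously does not fix two individuals for a trial that has recruited since 2018.

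That an article condenses a fuller protocol does not answer the point. The article devotes a section to the mechanism, and the mechanism it describes is what falls short.

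**Conclusion.** The concern holds in this form: the described mechanism does not secure concealment. It is not shown that concealment failed. Graduate students who collect consent and conduct the baseline WMCI look up the group themselves on a list generated in advance, and the stated safeguard does not keep later assignments from them. The main risks are consent at the visit and the conduct of the baseline WMCI; the self-reported EPDS and MAAS are less exposed.

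The size of any bias cannot be derived from the document. The one quantifiable part, 1.67 of 10 assignments certain from the fixed block, is secondary and rests on 1:1 blocks, knowledge of the block size and complete tracking of past assignments. The conclusion about the list rests on reading it as one that can show more than one line, which is the natural reading of {16b} and {16c} together.

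**What to change.** For women not yet randomized:

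1. Withdraw access to the list from recruiters, interviewers, coders and intervention teams.
2. Have the biostatistician release one assignment at a time, only after signed consent, baseline questionnaires and the first WMCI are logged as complete. A REDCap randomization module (REDCap is already in use) or sequentially numbered opaque sealed envelopes would serve equally.
3. Regenerating the remaining sequence with varying block sizes not disclosed to the site is optional once step 2 is in place. If it is done, state how the open block is closed. For example, if exactly 66 had been randomized, six blocks would be full and the seventh would have four places left.
4. Record the date of the change, and compare baseline EPDS and WMCI by arm before and after it, as a descriptive check.

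The cost is a short amendment, which the Ethics Committee must accept before it takes effect, and a small delay between the interview and disclosure of the group. Release should be prompt, because the three intervention visits are planned between 25 and 33 gestational weeks. No extra staff are needed. The change cannot undo any foreknowledge for women already randomized.
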